### Interventions

There are several strategies and/or interventions to improve male involvement in the PMTCT process described in the literature. These include psychosocial approaches, verbal encouragement, invitation letters, community education, and sensitization. A review performed by Takah et al [38] showed that psychosocial approaches and complex community interventions are more effective, whereas invitation letters are ineffective. Our review of the literature showed that home visits are one of the most effective single interventions, whereas multicomponent approaches could improve male involvement [14]. After a meticulous analysis of the literature on possible interventions, 3 different types of interventions were selected: (1) community sensitization through male champions; (2) special day for a male-friendly clinic; and (3) incentive to attend the clinical center addressing structural barriers. Each intervention will be performed in a selected center (Table 1).

**Table 1 table1:** The interventions.

Centers	Intervention	Ecological model levels	Activities
Kapire	Male Champions	Individual Interpersonal or social network Community	Individual counseling for men attending DREAM^a^ centers Home care for defaulting male patients Sensitization campaigns in local communities Sensitization campaigns in public spaces (churches, markets, clubs, and bars)
Balaka	Special Day	Individual Interpersonal or social network Health system	Basic health services: HIV testing and counseling Blood pressure measurement Counseling regarding cardiovascular disease Blood glucose measurement and counseling for diabetes Nutritional evaluation and counseling Group educational activities 2 educational sessions using the drama technique
Kapeni	Nudge	Individual Interpersonal or social network Structural	First visit Woman with partner: Food integration is given and an invitation card is delivered. If partners come for the second visit, they receive a second food integration Food integration is not given, but an invitation card is delivered, and if the male partner comes to the second visit, then the family receives a food pack Woman without a partner: Delivery food integration and registration that she has no partner Second visit with partner If the partner accompanies the woman to the center, the personnel will give a food package and offer couples counseling. The man can take advantage of individual services as educational contents

^a^DREAM: Disease Relief through Excellent and Advanced Means.

These strategies will be implemented according to standard clinical practices in Malawi with some modifications based on the international experiences described in the literature.

The *male champion* is a figure present in a few settings that conducts home visits with men and couples and follows up with men who did not accompany their partners to ANC visits [39]. Usually, this role is covered by the female expert clients, namely HIV-positive patients working in the organization as volunteers after appropriate training. Some men among patients who are receiving treatment will be identified and trained to cover this role [40]. The intervention called *male champion* aims to change the beliefs and attitudes of men, not intervening directly on individuals but upon entire communities and particularly involving community leaders.The *special day* is a practice that is becoming increasingly common to facilitate access to health facilities by vulnerable groups such as adolescents [41,42]. In this study, we target men. The special day takes place with an extraordinary opening of the clinical center once a month on a prefestive day (Saturday). During this day, access will be reserved exclusively for men, including those who are not on treatment for HIV. The center will offer free health promotion services to all participants. This intervention aims to remove the attitude linked to beliefs regarding masculinity, in which the male partners see access to health centers as an activity suitable only for women. The special day aims to make the clinical center more male-friendly and therefore attempts to overcome the social pressure that pushes men to have only sporadic attendance.The intervention based on the use of incentives (*nudge*) [43] to men who follow the prevention and treatment program aims to evaluate whether this action is effective in guiding behavior change toward the test, treatment, involvement, and adherence to therapy approach. The intervention defined as *budget* aims to remove the obstacles of a structural or a material nature, which supports the costs related to transportation to health care facilities and time taken away from work through a noneconomic incentive.

The educational tools developed for these interventions are based on standards adopted in the country for couples counseling on HIV/AIDS. To these standard guidelines, messages were added to initiate a reflective discussion of stereotypes and false beliefs related to the idea of masculinity in the Malawian culture. All staff involved in the delivery of these interventions were provided with a guide (included in Multimedia Appendix 1) on the contents to be delivered. They also participated in a one-day training of the themes of the project. The guide was developed by study investigators and Malawian health care staff. The guide was based on tools developed and applied in other contexts with the purpose of increasing men's access to health care services and to reduce stereotypes and gender-based violence. It was also based on the ecological model [44-49].

The educational content will be delivered using 3 different approaches. The *special day* arm will address the community in the catchment area of the clinical center, but the intervention will take place at the facility level. Through visibility activities such as leaflet distributions or information campaigns with audio messages, men living in the communities surrounding the treatment center will be invited to an extraordinary opening day at the center dedicated only to men. During the special day, the center’s clinical staff will offer basic health care services such as HIV testing and counseling, blood pressure measurement and counseling on cardiovascular disease, blood glucose measurement and counseling on diabetes, and nutritional evaluation and counseling. During the morning, group educational activities led by male community health care workers together with the doctors of the center and 2 educational sessions using drama techniques will be conducted. In the *male champions* arm, the intervention will be conducted at the level of regional and religious communities, with group educational sessions and use of the *male champions*. Male champions will be selected from patients receiving treatment for HIV for more than a year at the local DREAM centers. The educational sessions, based on an interactive approach with questions and answers both from the audience and the male champions, will last between 30 min to an hour. The male champion will be allowed to prolong the intervention if the audience requests it. Meetings will be planned and implemented in communities where at least five patients who receive treatment at DREAM centers reside, including religious communities in those regions. In the *nudge* arm, the intervention will be directed to individuals or to male partners of female patients being treated at DREAM centers. Women who agree to participate in the study will be asked to invite their male partners to the center for a health education session, and male partners who agree to participate will receive an incentive in the form of a food package, approximately worth US $8. At the second visit, the couple will be given a health education session based on educational materials prepared for the study.

The geographical locations of the 4 centers are shown in Figure 3. The centers are located at a distance that was considered sufficient to avoid geographical contamination. The 2 closest centers, Kapire and Balaka, are located at a distance of about 50 km; therefore, it can be reasonably excluded that patients can participate in both interventions. In any case, patients registered in the DREAM program and their family members are merged into a single database; therefore, the duplication of registration can be excluded.

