**Methods:**

The prospective, controlled before-and-after study is conducted in 3 phases (total duration: 24 months): preintervention, intervention, and postintervention analyses. The number of selected clusters (clinical centers) is limited to 4: one for each intervention, plus a cluster where no intervention is performed (control arm). The interventions are as follows: opening the facility on one Saturday per month only for men, defined as a *special day*; testing peer-to-peer counseling among men, *male champions*; and providing a noneconomic incentive to all women who are accompanied by their partners to the facility, *nudge*. The primary outcome of the study is to evaluate the differences in retention in care and adherence to therapeutic protocols among women; the intermediate outcome is the assessment of differences in male involvement. The level of male involvement in the health of their partners (intermediate outcome) will be evaluated through a dedicated questionnaire administered at baseline and in the postintervention phase. Data will be collected at the clinical centers and stored in 2 electronic databases managed using 2 different types of software.

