## Methods

### Strategy of the Study

The objective of the study is to evaluate 3 different interventions aimed at improving adherence and retention to ART therapy among HIV-positive women through engagement with their life partner. The interventions are (1) testing peer-to-peer counseling and community-level health education sessions delivered by men, *male champions*; (2) opening the facility once a month, only for men, *special day*; and (3) providing incentive to all women accompanied by their partners at the facility, *nudge* or *incentive*.

The different interventions to be implemented and evaluated in the research plan are designed to assess male involvement at the following levels, as depicted in the model represented in Figure 1. The activities that act on the individual and interpersonal or at the social network level common to past studies are transversal to all 3 interventions. At the individual level, both women and their male partners will receive educational content on the importance of retention and adherence to treatments, but also messages that contradict stereotypes and false myths related to masculinity, health, and gender violence. With regard to the interpersonal or social network level, all interventions will include support activities that are aimed at the family (couples counseling).

*Intervention 1* (*Male Champions*) will act at the community level, providing educational interventions that are aimed at territorial communities and religious groups.*Intervention 2* (*Special Day*) will act at the health system level, delivering activities based on health facilities that are aimed at reshaping the clinic as male-friendly.*Intervention 3* (*Nudge*) will also act at the structural level by providing incentives to support the cost of transportation and other costs that reduce a male partner’s ability to access the service.

The study has 3 phases: preintervention (baseline), intervention, and postintervention analyses, as shown in Figure 2.

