The centers represented the Malawian population. As Malawi is a country where 83% of the population resides in rural or semirural environments [35], rural clinics were selected.Centers that only provided maternal services were excluded because it was not possible to use a male-friendly approach in a center that is designed to accommodate only women.The remaining centers with the highest number of female patients were selected.

The *special day* intervention was assigned to the center of Balaka (Balaka district). At this site, health care staff are available to offer the planned services. The *male champion* intervention was assigned to the Kapire center (Machinga district), where there are patients available to engage themselves as male champions who have sufficient levels of education necessary to perform the task assigned to them and communicate with the researchers. The *nudge* intervention was assigned to the Kapeni center (Blantyre district), where the number of women being treated was consistent with the available budget necessary for the provision of noneconomic incentives.

Although the unit of analysis is the clinical center, and therefore all patients who are referred, the study focuses on the population of adult females and the influence of male partners on the health practices of women. Therefore, data will be collected from this specific population. Eligibility criteria for women included the following: being HIV positive; inclusion in an HIV/AIDS prevention and treatment program; aged 18 years or older; and living at home with a male partner.

There are several possible criteria for defining a partnership relationship. In the Malawian context, the concept of marriage is understood in many different ways depending on local tradition or different religious practices [36]. Furthermore, mobility is quite high and there are situations in which the married partner spends longer periods away from the family or abroad; therefore, there is no possibility of directly influencing his wife's health practices. Hence, in this study, it was decided to consider the man who resides in the same house with the woman as a partner, regardless of religious or legal bonds between the two.

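### At the nudge center, Table 1's food rules could reward a woman for reporting no partner, and that report takes her out of the accompaniment denominator

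*Protocol article*

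**What the plan says.** All references are to the protocol article.

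- **Food rules.** Table 1 (Interventions) has two lines for a partnered woman's first visit at Kapeni. On the first, "Food integration is given and an invitation card is delivered", with more food if the partner comes to the second visit. On the second, "Food integration is not given, but an invitation card is delivered, and if the male partner comes to the second visit", the family then receives a food pack. For a woman without a partner the entry is "Delivery food integration and registration that she has no partner". No invitation card is mentioned for her.
- **Purpose of the incentive.** The Abstract describes "providing a noneconomic incentive to all women who are accompanied by their partners to the facility", and Strategy of the Study describes "providing incentive to all women accompanied by their partners at the facility". The text of Interventions says that male partners who agree to take part "will receive an incentive in the form of a food package, approximately worth US $8".
- **Eligibility.** Setting and Participants requires women to be "aged 18 years or older; and living at home with a male partner". A partner is the man who shares the house. Clinicians check the entry criteria at the visit; the only software flag described concerns age.
- **Indicator.** Outcomes and Statistical Methods lists, as a measure of male involvement (the intermediate outcome), the share of women whose partner came with them once they had been given an invitation card.
- **Phases.** Participants are the women attending in the pre- and postintervention phases. Results dates the end of baseline enrollment to March 31, 2020, and has the interventions under way as of August 1, 2020.

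**The concern.** Three rules that look harmless one by one interact. Reporting no partner brings food immediately. Under one of the two lines for partnered women, reporting a partner brings food only if he attends. Reporting no partner also makes the woman ineligible and, since Table 1 mentions a card only for partnered women, takes her out of the accompaniment denominator.

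The women with the most reason to report no partner are those who expect him not to come, and these are the women who would otherwise count as unaccompanied. If some do so, the Kapeni figure rises although no man has changed his behavior. No other center has a food rule tied to partner status, and the rule did not exist during baseline enrollment. The distortion would therefore sit in one center and one phase. A before-and-after comparison at Kapeni would not remove it, and neither would a comparison of changes with the control center. The study means to name the best of three interventions, so a bias that can favor only one of them matters.

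**Working it through.** **Inputs from the article.** Baseline enrollment is 133 + 78 + 75 + 166 = 452, which reproduces the stated total. Kapeni contributes n = 78. Design of the Study and Theoretical Framework gives male involvement in Malawi as 3.2% to 23%. The stated significance level is 0.04.

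**Assumptions.** The article gives no accompaniment proportion for Kapeni and no rate of no-partner registration. I assume 78 women in the postintervention phase, a = 16 truly accompanied, and k of the 62 unaccompanied women registered as having no partner.

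**Formula.** The true proportion is a/n. The observed proportion is a/(n−k). Their ratio is n/(n−k), which does not depend on a.

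| k | Share of the 62 | Observed proportion | Gain (points) | Ratio |
|---|---|---|---|---|
| 0 | 0% | 16/78 = 20.5% | 0 | 1.00 |
| 10 | 16% | 16/68 = 23.5% | 3.0 | 1.15 |
| 20 | 32% | 16/58 = 27.6% | 7.1 | 1.34 |

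**Across the article's range of involvement.** Near the top, 18/78 = 23.1% becomes 18/70 = 25.7% with k = 8 and 18/62 = 29.0% with k = 16. Near the bottom, 2/78 = 2.6% becomes 2/62 = 3.2% with k = 16, a negligible change in points.

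**False-positive rate.** In a simulation of 200,000 runs, a pre/post chi-square test at 0.04 compared 78 women per phase with no change in behavior. A fixed share of unaccompanied women was removed in the post phase only. At a true proportion of 23%, the rejection rate was 0.040 with none removed, then 0.048, 0.076, 0.133 and 0.232 with 10%, 20%, 30% and 40% removed. At a true proportion of 10%, the rates for the same four shares were 0.043, 0.059, 0.089 and 0.145.

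**Retention.** An effect here needs a further assumption. Suppose 23% of partners are involved, with dropout of 10% among their women and 25% among the rest.
- Overall dropout is 0.23 × 10% + 0.77 × 25% = 21.6%.
- With 40% of the women with uninvolved partners removed, the involved share becomes 0.23/(0.23 + 0.77 × 0.6) = 33.2%, and dropout becomes 0.332 × 10% + 0.668 × 25% = 20.0%.
- If dropout is equal in the two groups, it does not move at all.

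**The case against.** The strongest objection is that the motive rests on one line of a table cell. Under the other line a partnered woman receives food at once and may receive more, so she gains nothing by denying a partner. Layout may also have been lost: the first line may be meant for couples who attend together and the second for women who come alone. This limits the point but does not remove it. The article states no condition separating the lines, and on the couples-versus-alone reading the withholding line would apply to the very women at issue.

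Second, the described order offers some protection. Entry criteria are checked before the medical examination, and women who have agreed to take part are then asked to invite their partners. Nothing says that a later no-partner registration removes an enrolled woman. On this reading she would have to know the rule beforehand, for instance by word of mouth. That is fair. However, Table 1 also places the no-partner registration at the first visit, and the article does not say which step comes first. Clinicians know their patients, and the program database includes family members, but neither is described as a check on partner status.

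Third, every value of k is assumed and small values do little. This stands in full.

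Fourth, the Abstract and Strategy of the Study do not say that only accompanied women receive food, so food for women outside the study population need not contradict them. This stands in part. The clearer inconsistency is between the two lines for partnered women.

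A reader might go further and infer that separations after an invitation hide violence from the violence score. The documents do not support this as part of the point: the cohabitation criterion applies at every center and in both phases, and nothing shows that partners leave because they were invited.

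**Conclusion.** The point holds as a possibility created by the stated rules. At Kapeni, once the nudge is running, misreported partner status could raise the accompaniment indicator by a factor of n/(n−k), and neither baseline nor control would correct it. With 16 of 78 accompanied, that is 3.0 points for k = 10 and 7.1 points for k = 20. These figures rest on an assumed accompaniment proportion, an assumed k, and the withholding line of Table 1 applying to the women concerned.

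A reader might infer that the postintervention sample at Kapeni is in fact enriched for cooperative partners, or that retention and adherence will look better there. The article supports neither inference. It shows that the route is open, not that anyone takes it. An effect on the primary outcomes needs the added assumption that women with uninvolved partners do worse. The Introduction argues in that direction, but even then the worked example moves dropout by only 1.6 points under 40% removal.

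**What to change.** 1. Record cohabitation status in the same way at all four centers before the food rule is explained, using the baseline enrollment record where one exists.
2. Keep women recorded as cohabiting who later register no partner in the accompaniment denominator and in follow-up for retention and adherence. Add a sensitivity analysis that excludes documented separations, since some changes of status will be genuine.
3. Report the number and share registered as having no partner, by center and phase. An excess at Kapeni in the postintervention phase would be the signal to look for.
4. Reconcile Table 1's two lines for partnered women, and its no-partner line, with the Abstract, Strategy of the Study and the text of Interventions. This review does not say which food rule is right.

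The cost is one field recorded earlier in the visit, some wording on eligibility and denominators, and possibly a less favorable figure for the nudge. Reanalysis at the end cannot recover women who were never enrolled, so the recording has to change during enrollment.

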**Figure 3 figure3:**
[figure not shown]
Geographical location of the 4 clusters.

### Outcomes and Statistical Methods

The outcomes will be divided into 2 levels: (1) evaluation of the variations in retention in care and women's adherence to therapeutic protocols (primary outcome) and (2) assessment of the variations in male involvement (intermediate outcome).

Retention in care and adherence to treatment protocols are primary outcomes. Retention in care will be measured as the cumulative proportion of dropouts from the treatment program at 6 months, 1 year, and 2 years (excluding patients transferred to another center or those who died). Adherence will be measured through the following indicators: (1) the cumulative proportion of medical appointments missed in a month in the center; (2) the cumulative proportion of appointments for drug delivery missed in a month in the center; (3) the cumulative proportion of women who suppressed viral load; and (4) the cumulative proportion of women with a suppressed viral load that has a rebound in viremia.

To evaluate the level of male involvement in the health of female partners (intermediate outcome), a dedicated questionnaire will be delivered to female partners at baseline (preintervention) and in the postintervention phase. The survey measures the following outcomes related to male involvement: (1) proportion of women accompanied by partners at the facility after receiving an invitation card; (2) proportion of men accepting HIV testing and counseling (if not yet received in the last 6 months); (3) level of partner involvement in the care process measured through a score scale based on health practices reported by the female partners; and (4) level of gender-based violence in the family measured through a score scale based on violent or negative practices reported by female partners.

Some indicators will be collected to monitor the delivery of the intervention and possibly evaluate correlations with the dose of delivery of the 3 interventions, as outlined in Textbox 1.

The primary and secondary indicators of effectiveness are the same for all interventions, hence making it possible to assess the differential impact of the community, health system, and structural-level interventions, particularly with respect to interventions based only on individual and interpersonal levels. These interventions will be compared with the usual services offered at the fourth center.

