In the preintervention analysis, the baseline situation of the 3 participating centers will be evaluated. The aim of this phase is to set a starting point to weigh the relative effect of each intervention to be studied. For that purpose, baseline data of each study site will be collected. To evaluate the effect of the interventions, the same indicators will be measured during the pre- and postintervention phases, as described above. The preintervention phase will last 9 months. During this period, data will be collected at each site and included in a database.

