## Results

The enrollment of patients in the preintervention phase started in July 2019 and ended on March 31, 2020. There is an ongoing analysis of preliminary data collected at the 4 centers during the preintervention phase. In total, 452 female participants were enrolled in the preintervention phase, with the following distribution: Namandanje (n=133); Kapeni (n=78); Kapire (n=75); and Balaka (n=166). Several meetings have been performed at the centers to organize the intervention phase. As of August 1, 2020, the interventions were initiated at the 3 centers and by September 2020 were ongoing.

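### Two-year retention cannot be compared before and after intervention within a 24-month study, and on the stated dates one-year retention does not fit either

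*Protocol article*

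**What the plan says.** The Outcomes and Statistical Methods section names retention as a primary outcome and defines it so: "Retention in care will be measured as the cumulative proportion of dropouts from the treatment program at 6 months, 1 year, and 2 years". It names no time origin. The Strategy of the Study section makes this a before-after comparison, since "the same indicators will be measured during the pre- and postintervention phases".

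The calendar is given in three places:

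- Abstract, Methods: the study is "conducted in 3 phases (total duration: 24 months): preintervention, intervention, and postintervention analyses".
- Strategy of the Study: "The preintervention phase will last 9 months".
- Results: "The enrollment of patients in the preintervention phase started in July 2019 and ended on March 31, 2020", and then "As of August 1, 2020, the interventions were initiated at the 3 centers and by September 2020 were ongoing".

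The text gives no length for the intervention or postintervention phase and no date on which follow-up ends. It does not say whether the 24 months were extended for the gap between the end of preintervention enrollment and the start of the interventions.

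**The concern.** A before-after contrast at a given horizon needs women followed that long without the intervention and women followed that long with it. A horizon equal to the whole length of the study leaves no room for both. Two of the three primary retention horizons are affected: 2 years certainly, and 1 year on the dates given.

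If the longer horizons are calculated anyway, follow-up from the intervention period is counted as before, or time that precedes the intervention is counted as after. The resulting contrast would then not measure what the interventions did, although it would be reported as a primary result.

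**Working it through.** **Inputs.** Total duration 24 months (Abstract, Methods). Preintervention phase 9 months (Strategy of the Study). Preintervention enrollment July 2019 to 31 March 2020, interventions from 1 August 2020, and baseline numbers Namandanje 133, Kapeni 78, Kapire 75, Balaka 166 (Results). Months are days divided by 30.4375. The day in July 2019 is not given, so 1 July and 31 July are used as limits.

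**The article's own figure.** 1 July 2019 to 31 March 2020 is 9.0 months, which reproduces the stated 9.

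**After side: time available under intervention**

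- As planned: 24 − 9 = 15 months for the intervention and postintervention phases together.
- On the stated dates, start 1 July 2019: month 24 is 1 July 2021, and 1 August 2020 to 1 July 2021 is 11.0 months.
- On the stated dates, start 31 July 2019: month 24 is 31 July 2021, which gives 12.0 months. This is the limit case, and it applies only to follow-up that begins on the first day of the interventions.
- If the roughly 4-month gap (April to July 2020) is added to the 24 months, which is an assumption: about 15 to 16 months.
- Twelve exposed months need follow-up to about 1 August 2021 (study month 25, counted from 1 July 2019). Twenty-four need about 1 August 2022 (study month 37).

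**Before side: unexposed time from enrollment to 1 August 2020**

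- Enrolled in July 2019: 12.1 to 13.0 months.
- Enrolled on 31 March 2020: 4.0 months.
- Mean under even enrollment: (13.0 + 4.0) / 2 = about 8.5 months.

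**How many baseline women pass each horizon on or after 1 August 2020.** Assume even enrollment over 1 July 2019 to 31 March 2020 (275 days), at the three intervention centers: 78 + 75 + 166 = 319 women.

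- Month 6: enrolled on or after 1 February 2020, 60/275 = 21.8%, about 70 of 319.
- Month 12: enrolled on or after 1 August 2019, 244/275 = 88.7%, about 283 of 319.
- Month 24: all 319, since the longest unexposed time is 13.0 months.

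**Clock started at program entry instead.** With at most 12 exposed months by the end of the study, a woman's first 2 years in the program contain at least 24 − 12 = 12 unexposed months, which is half. With the assumed extension to 16 months it is still at least 24 − 16 = 8 months, a third.

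| Horizon | Unexposed from enrollment (4 to 13 months) | Exposed, stated dates (11 to 12 months) | Exposed, if extended (15 to 16 months) |
|---|---|---|---|
| 6 months | most women | fits from intervention start | fits |
| 1 year | only the earliest enrolled | limit case only | fits from intervention start |
| 2 years | none | none | none |

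**The case against.** The strongest reply is that the retention clock is not stated. The outcome concerns leaving the treatment program, the women are already in such a program when they join the study, and clinical data are held routinely in DREAM_S. Counted from program entry, proportions at all three horizons could be calculated in both phases. This stands to the extent that a reader who infers that the longer-horizon figures cannot exist goes too far. It does not rescue the contrast. On the stated dates at least half of the 2-year window precedes the intervention. Women are also recruited when they attend a visit, so those who join 2 or more years after entry are, barring interruption and return, already known to have been retained.

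A second reply is that the end date is inferred and the phase diagram is not visible. This also stands in part. With an extension for the 2020 gap, 1 year becomes reachable from intervention start, so the documents do not support calling 1-year retention impossible without qualification. No variant reaches 2 years.

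Three other inferences are tempting and unsupported:

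- **Counting all 452 baseline women as affected.** The 133 at Namandanje, which received no intervention, are never exposed.
- **Saying that most of the 1-year baseline window is contaminated.** Mean unexposed time is about 8.5 of 12 months. The 89% counts women whose 12-month point falls late; it is not a share of follow-up time.
- **Claiming that the bias must run toward no effect.** Differences in time already spent in the program, or survivorship among women already in care, could move the contrast either way.

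The planned Cox regression can accommodate censoring, so contamination of the before period is avoidable. The article has not yet said that it will be avoided.

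**Conclusion.** The stated horizons and the stated calendar conflict. With time counted from enrollment or intervention start, the 2-year before-after contrast cannot be obtained in any calendar variant: exposed follow-up is at most 11 to 12 months on the stated dates, 15 as planned, and about 15 to 16 with an extension, while unexposed follow-up is at most 13. The 1-year contrast does not fit the stated dates outside the limit case, and only the earliest enrolled women supply a full unexposed year. With time counted from program entry, the 2-year figure is computable but does not measure the intervention. The 6-month horizon is sound on the after side when counted from intervention start. On the before side about 70 of 319 women need censoring.

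The calendar result rests on the dates in the article alone. The counts of 283 and 70 also assume even enrollment at the three intervention centers. The 15-to-16-month figure assumes an extension that the article does not state.

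**What to change.** Make 6-month retention the primary before-after retention horizon. Use the same time origin in both phases, namely study enrollment in that phase, and identical 6-month windows. Censor preintervention follow-up at 31 July 2020 at all four centers; the control center is included so that calendar periods match. State the date on which follow-up ends. For complete 6-month windows, postintervention enrollment must close 6 months before that date. If month 24 falls on 1 to 31 July 2021, that means closing by 1 to 31 January 2021.

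Report 1- and 2-year retention only as descriptive long-term follow-up from routine records, and restore 1 year as a contrast only if the end of the study is extended.

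The cost is mainly a change of text, since retention can be followed in the routine clinical records, together with giving up the claim of a longer-term effect. Redefining the after group as every woman on a center's register from 1 August 2020 would be a larger change. The documents do not say that DREAM_S records whether a woman lives with a partner, or that women outside the study consented. Keeping enrollment in each phase as the origin avoids that problem.
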